#### Primary objectives

To find out the time to recover after surgery following TLH, NDVH and TAH.To calculate the total cost per surgery from a societal perspective for TLH, NDVH and TAH.To compare the cost-effectiveness of TLH versus NDVH versus TAH.

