### Description of study instruments

The validated paper-based Sinhala and Tamil EQ-5D-3L questionnaire will be used to obtain health utility scores. The EQ-5D-3L is a generic multi-attribute utility system, which assess health-related quality of life on five dimensions (mobility, self-care, usual activities, pain/discomfort, anxiety/depression) [17]. Based on the responses a woman will be placed in to one of 243 (3^5^) mutually exclusive health states, and a value for each of these has previously been estimated with ‘0’ being equivalent to dead and ‘1’ being equivalent to perfect health on a utility scale based on interviews. EQ-5D 3L questionnaires will be administered 1 day preoperatively and on postoperative day 2, 1 week, 6 weeks, 3 months and 6 months postoperatively. Each woman’s QALYs will be calculated using the utility score and the time spent on the particular health state. A utility value table specific to Sri Lanka will be used to calculate QALYs [18].

Urinary and sexual function will be assessed by the validated Sinhala and Tamil translations of International Consultation on Incontinence Modular Questionnaire on Female Urinary Tract Symptoms (ICIQ-FLUTS) and Incontinence Modular Questionnaire on Vaginal Symptoms ICIQ-VS which were obtained from the International Consultation on Incontinence (ICI) [19–21]. Bowel symptoms will be assessed by a questionnaire based on a study done by Tharkar et al. [22]. These questionnaires will be used preoperatively, 6 months and up to 1 year post-hysterectomy to detect changes in pelvic organ function.

Postoperative pain evaluation will be done using numeric pain rating scale (NRS) [23], asking the patient to indicate the intensity of current, best, and worst pain levels over the past 24 hours on a scale of 0 (no pain) to 10 (worst pain imaginable). The average of the three ratings; average, best, and worst will be used to represent the patient’s level of pain over the previous 24 hours. To allow direct comparison of pain medication a modified World Federation of Societies of Anaesthesiologists (WFSA) analgesic ladder will be used [24].

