### Data analysis

All randomized patients will be included in the analyses. A single principal analysis will be done comparing the three arms (TAH, NDVH and TLH) 12 months after the last woman has had her operation. The fact that the trial will be conducted at two centres will be taken into account during data analysis.

A Kaplan–Meier survival analysis will be done for the primary outcome which is time to recover following hysterectomy. The end-point is the actual time to recover. It will be assessed and documented at the 6-week clinic visit. Patients who have not recovered by 6-weeks will be followed-up beyond 6-weeks to detect complications and the actual time to recover. Post hoc pairwise analysis between TAH, NDVH and TLH will be done using COX regression.

Other outcomes that need follow-up; QALYs, urinary, vaginal and bowel functions will also be analysed using Kaplan Meier survival analyses. The end point for QALYs is 6-months while for urinary, vaginal and sexual function it is 1-year. Patients who do not complete follow-up in these secondary outcomes will be right censored up to their respective end-points. Post hoc pairwise analysis between TAH, NDVH and TLH will be done using COX regression. The other outcomes; operative time, anaesthesia time, postoperative hospital stay, cost, pain scores and blood loss will be analysed using Kruskal-Wallis test with post hoc comparisons. The complications will be described for each category. A fully specified Statistical Analysis Plan will be provided before opening the database.

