### Economic evaluation

The economic evaluation will take societal perspective and will include direct costs related to utilization of healthcare resources in the hospital and indirect costs which are borne by the patient. A micro-costing approach will be adopted to calculate utilization of hospital resources from the time of presentation to the gynaecology clinic up to six months after surgery. Incremental cost-effectiveness ratios (ICER) will be obtained by calculating the incremental costs divided by the incremental effects (time to recover and QALYs gained) for the intervention groups (NDVH and TLH) over the standard care (TAH) group.

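### Preoperative EQ-5D-3L and pelvic-function scores are collected, but the named analyses give them no role, which costs precision in the QALY difference behind the ICER

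*Protocol article*

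**What the plan says.** One of the three primary objectives is "To compare the cost-effectiveness of TLH versus NDVH versus TAH". The Economic evaluation section defines the measure: "Incremental cost-effectiveness ratios (ICER) will be obtained by calculating the incremental costs divided by the incremental effects (time to recover and QALYs gained"), with NDVH and TLH each set against TAH.

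On the utility data, the section Description of study instruments gives the schedule: "EQ-5D 3L questionnaires will be administered 1 day preoperatively and on postoperative day 2, 1 week, 6 weeks, 3 months and 6 months postoperatively". It then says how one woman's QALYs are built: "Each woman’s QALYs will be calculated using the utility score and the time spent on the particular health state". The urinary, vaginal/sexual and bowel questionnaires are also completed before surgery, then at 6 months and up to 1 year, with the declared purpose of detecting change.

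On the comparison between arms, Data analysis says "QALYs, urinary, vaginal and bowel functions will also be analysed using Kaplan Meier survival analyses", with pairwise Cox regression to follow, and "The end point for QALYs is 6-months". The two centres are to be allowed for in the analysis. No baseline score is named as a covariate anywhere. The section closes with a promise: "A fully specified Statistical Analysis Plan will be provided before opening the database". That plan is not at hand.

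**The concern.** A baseline measurement of the outcome is usually the most useful covariate a trial has. Here it is collected for utility and for all three pelvic-function domains, but the stated analysis does not use it.

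This matters most for QALYs. If preoperative utility predicts later utility, a chance difference between arms before surgery carries through the 6-month area under the curve and appears as QALYs gained or lost. The trial is small for a utility outcome. The QALY gain that follows from its own 7-day recovery target is also very small, so the denominator of the ICER lies close to zero and noise from baseline imbalance can be of the same order as the effect.

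The named methods do not solve this. Kaplan-Meier takes no baseline covariate. Cox regression could take one, but none is stated, and its output is a hazard ratio. Neither gives the mean QALY difference that the ICER needs.

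**Working it through.** **Reproducing the plan's sample size.** Inputs from Sample size calculation: difference 7 days, SD 9.5 (TAH) and 8.5 (VH), two-sided alpha 0.01, power 80%, loss 20%.

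- Pooled SD = sqrt((9.5² + 8.5²)/2) = sqrt(81.25) = 9.01.
- n = 2 × (2.576 + 0.842)² × 81.25 / 7² = 38.7, so 39 per arm.
- 39 / (1 − 0.20) = 48.75, so 49 per arm and 147 in total, as stated.

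About 39 women per arm are therefore expected in the analysis.

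**Assumed inputs.** The article gives none of these:

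- SD of preoperative utility: 0.2, with a range of 0.1 to 0.3.
- Slope b of mean follow-up utility on preoperative utility: 0.1, 0.25 or 0.5.
- Utility gap between recovered and not recovered: 0.2 to 0.3.

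**Benchmark effect.** Seven days' faster recovery is worth 7 × gap / 365.25: 0.0038 QALY at a gap of 0.2 and 0.0057 at 0.3.

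**Carry-over of chance imbalance.** The SE of the baseline utility difference is SD × sqrt(2/39): 0.023, 0.045 and 0.068 for SD 0.1, 0.2 and 0.3. A one-SE imbalance moves the 6-month QALY difference by 0.5 year × b × SE. At SD 0.2:

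| Slope b | Carry-over (QALY) | Chance it reaches 0.0038 | Chance it reaches 0.0057 |
|---|---|---|---|
| 0.1 | 0.0023 | 0.09 | 0.01 |
| 0.25 | 0.0057 | 0.50 | 0.31 |
| 0.5 | 0.0113 | 0.74 | 0.61 |

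The chance is 2 × (1 − Φ(effect / carry-over)). Over SD 0.1 to 0.3 and b 0.1 to 0.5, the one-SE carry-over runs from 0.0011 to 0.0170.

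**Where the carry-over comes from.** With assessments at days −1, 2, 7, 42, 91 and 182.5, the baseline value has a trapezoid weight of 1.5 of 183.5 days, or 0.8%. Almost all the carry-over therefore depends on b.

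**What adjustment gains.** Regression on baseline multiplies the SE of the QALY difference by sqrt(1 − rho²), where rho is the correlation between preoperative utility and 6-month QALYs. The factor is 0.954 at rho 0.3 (about 5% lower) and 0.866 at rho 0.5 (about 13% lower). If mean follow-up utility also has SD 0.2, the QALY SD is 0.5 × 0.2 = 0.1 and the unadjusted SE is 0.1 × sqrt(2/39) = 0.0226. It falls to 0.0216 at rho 0.3 and 0.0196 at rho 0.5.

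**The case against.** The strongest objection is that this is silence in a condensed article, not an error. The Economic evaluation section defines a ratio and does not say how either increment is estimated; an adjusted difference fits the sentence as well as an unadjusted one. Covariates are commonly left to the analysis plan, and one is promised. Much of this stands. A reader might infer that the plan commits to a raw difference in QALYs, but nothing in the text says so or rules out adjustment. What remains is that Data analysis does not leave the method open: it assigns QALYs and the pelvic-function scores to methods that make no stated use of baseline and do not supply the mean difference. An analysis plan that simply expanded this text would be unadjusted.

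The size is also open to challenge, and this stands too. It rests on assumed values. A slope near 0.1 is possible because surgery treats the cause of the preoperative symptoms, and the carry-over is then minor. The benchmark counts only a week's faster recovery; a utility difference from complications, pain or pelvic function that lasted longer would make the effect larger.

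Two stronger readings are tempting. One is that baseline imbalance biases the ICER. Under randomisation it adds variance only. The other is that adjustment would settle the sign of the QALY difference. With a true effect of 0.0057, the chance of a wrong sign is Φ(−0.0057/0.0226), about 40%, without adjustment and Φ(−0.0057/0.0196), between 38% and 39%, at rho 0.5. The main difficulty is a small sample against a tiny effect. Nor can the gain be expressed as power by borrowing the 7-day effect and SD of 9.0: time to recover has no baseline measurement and is analysed by Kaplan-Meier and Cox.

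**Conclusion.** The point holds as a matter of efficiency and of fixing the estimator. Baseline utility and pelvic-function scores are collected, no adjustment for them is named, and the methods named neither use them nor produce the QALY difference that a primary objective requires.

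At 39 per arm, SD 0.2 and slope 0.25 to 0.5, a one-SE imbalance is worth 0.006 to 0.011 QALY, against 0.004 to 0.006 for the recovery benchmark. The comparison is conditional on the assumed SD, slope and utility gap, and it largely disappears at slope 0.1. The gain from adjustment is a modest reduction in SE, 5% to 13% for rho 0.3 to 0.5. It would not rescue an underpowered QALY comparison. The change is still worth making because it uses data in hand, and because settling it before the database is opened prevents a later choice between adjusted and unadjusted ICERs.

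**What to change.** In Data analysis and Economic evaluation, and in the promised analysis plan, state that:

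- incremental 6-month QALYs will be estimated by linear regression on arm, preoperative EQ-5D-3L utility and centre, since randomisation is carried out separately at each site;
- the adjusted difference will enter the ICER, with the unadjusted difference shown beside it;
- the 6-month and 1-year urinary, vaginal/sexual and bowel scores will be compared with the corresponding preoperative score as a covariate.

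The cost is a few sentences and no new data. There is one small downside. The preoperative form is completed the day before surgery in a trial where patients and staff are not blinded, and the article does not say whether allocation is known by then. Knowledge of the allocation could colour the baseline answers, which is a further reason to report both results.

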Most comparative studies on hysterectomy are between two approaches; vaginal versus laparoscopic, abdominal versus laparoscopic or vaginal versus abdominal [2–6]. These studies and even systematic reviews are underpowered to detect a difference in major complications such as visceral injuries between the three main methods [2–7]. Although initial studies suggested an increased risk of urinary tract damage in TLH, the risk may not be that high now when the effects of the learning curve of laparoscopy and the evolution of the technique of TLH are considered [8]. Although direct costs appear to be high for TLH, a shorter postoperative hospital stay and lower indirect costs appear to make it more cost-effective compared to the standard TAH [4, 5, 9, 10]. There is evidence to suggest that VH appears to be less costly compared to LH according to the eVALuate trial [11]. However to date, there has been no direct comparison of costs between VH and TAH. Neither has there been any study which has attempted to shed light on the costing of hysterectomy in developing countries, where the emphasis should be on cost-effectiveness. Cost of healthcare interventions is an important aspect to consider in limited-resource settings. Although free public healthcare is available in Sri Lanka, it is important to know the cost incurred due to the huge burden on taxpayers. Therefore, direct health sector-related costs should be explored if cost-effectiveness is the ultimate aim, especially for a low- and middle-income country. Indirect costs incorporating loss of productivity are important, especially when the target population involves the population workforce, to get a wider perspective of costs incurred. Against such a backdrop, an ideal costing study would need to involve a broader societal perspective considering direct costs related to the health sector and indirect costs incorporating recovery-related costs and loss of productivity.

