### Objectives

We hypothesize that TLH and NDVH are better than TAH in terms of time to recover, quality-adjusted life years (QALYs), pelvic organ function and cost-effectiveness. It will have the added advantage of providing valuable information on health-related quality of life, pelvic organ function and costing for the commonest gynaecological major surgical procedure.

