### Outcome measures

The primary outcome is time to recover following hysterectomy (earliest time to resume all or a combination of activities done prior to surgery; resumption of cooking, washing clothes, sexual activity and occupation). The secondary outcomes are operative time (skin to skin), postoperative hospital stay, anaesthesia time, complications (bladder injury, ureteric injury, bowel injury, convert to laparotomy, vault haematoma, blood transfusion, postoperative fever, skin wound infection, urinary tract infection, respiratory tract infection, deep vein thrombosis/pulmonary embolism, re-operation), postoperative pain and total pain medication per day per patient, QALYs, urinary, sexual and bowel function and total cost per surgery. The outcome measures are shown in Table 1.

**Table 1 Tab1:** Outcome measures and study instruments

Outcomes	Study instrument
Time to recover	Patient filled data sheet at 6 weeks
Operative time	Data sheet on operative period filled by research assistant.
Postoperative hospital stay	Postoperative data sheet filled by research assistant
Cost	Direct costs based on preoperative, operative, postoperative, 6-week and 6-month data sheets filled by research assistant Indirect costs based on preoperative, postoperative, 6-week and 6-month data sheets filled by patient
Complications	Data sheet on operative, postoperative, 6-weeks and 6-months period filled by research assistant
Anaesthesia time	Data sheet on operative period filled by research assistant
Pain scores and pain medication	Data sheet on postoperative period filled by research assistant
Blood loss/change in haematocrit	Data sheet on operative and postoperative period filled by research assistant
QALYs	Paper-based EQ-5D-3L (Sinhala/Tamil) [16]
Urinary function	ICIQ-FLUTS (Sinhala/Tamil) questionnaire [18, 19]
Vaginal and sexual function	ICIQ-VS (Sinhala/Tamil) questionnaire [20]
Bowel function	Bowel symptoms questionnaire [21]

*EQ-5D-3L* EuroQoL group questionnaire on health-related quality of life, *ICIQ-FLUTS* International Consultation on Incontinence modular Questionnaire on Female Lower Urinary Tract Symptoms, *ICIQ-VS* International Consultation on Incontinence modular Questionnaire on Vaginal Symptoms, *QALYs* Quality-adjusted life years

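### The recovery-time ICER divides cost by a raw duration, so its sign runs opposite to the QALY ICER for a better route, and ratios against TAH alone do not answer the three-way primary objective

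*Protocol article*

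**What the plan says.** The Economic evaluation section defines the ICER as the result of "calculating the incremental costs divided by the incremental effects (time to recover and QALYs gained"). Each ratio sets one of the two newer routes, NDVH or TLH, against TAH as the comparator. The abstract gives the same definition. The word 'gained' is attached to QALYs only.

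Under Outcome measures, time to recover is the "earliest time to resume all or a combination of activities done prior to surgery", so a smaller value is a better result. The Objectives section confirms the direction: "We hypothesize that TLH and NDVH are better than TAH in terms of time to recover".

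The primary objectives include a cost-effectiveness comparison among all three routes. The Sample size calculation section gives planning means of 28.1 days (TAH), 21.3 days (VH) and 19.7 days (LAVH). It gives no figure for TLH itself. The article states no cost, QALY difference or value per day or per QALY. The Data analysis section announces a full statistical analysis plan, which is not shown.

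**The concern.** An ICER is normally read as the price of one more unit of benefit. That reading needs an effect that rises as patients do better. Time to recover falls as patients do better, so its ratio has the reversed sign. The trial would then report two ICERs for the same route under opposite conventions. A dearer route that is better on both effects would show a negative cost per day and a positive cost per QALY. A reader who takes a negative ICER as a sign of dominance would misread the first.

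Two further matters bear on the same primary objective. A ratio alone does not say which quadrant of the cost-effect plane a route occupies. And two ratios that share the TAH comparator do not say whether TLH is worth its cost relative to NDVH.

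**Working it through.** **Inputs.** From the Sample size calculation section: means of 28.1 (TAH), 21.3 (VH) and 19.7 (LAVH) days; SDs of 9.5 (TAH) and 8.5 (VH); difference to detect 7 days; two-sided type 1 error 0.01; power 80%; loss 20%. Assumed, because the document gives none: a cost difference of 100 units (range 50 to 200), a QALY difference of 0.01, and a value of 20 units per recovery day saved.

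**The plan's own figure.** The document states no ICER. Its sample size does reproduce. The TAH-VH SD is sqrt((9.5² + 8.5²)/2) = 9.014, and a 7-day difference needs 39 per arm. Then 39/(1 - 0.2) = 48.75, which rounds up to 49 per arm and 147 in total. The point does not depend on this, but it shows the planning data are read as intended.

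**Step 1: increments in time to recover, route minus TAH.**
- VH: 21.3 - 28.1 = -6.8 days
- LAVH: 19.7 - 28.1 = -8.4 days

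**Step 2: signs of the ratios**, with a difference of 6.8 days, 100 cost units and 0.01 QALY. Net benefit = 20 × days saved - incremental cost.

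| Route versus TAH | Cost increment | Raw days | Cost / raw days | Cost / QALY | Cost / days saved | Net benefit |
|---|---|---|---|---|---|---|
| Cheaper, better | -100 | -6.8 | +14.71 | -10,000 | -14.71 | +236 |
| Dearer, better | +100 | -6.8 | -14.71 | +10,000 | +14.71 | +36 |
| Cheaper, worse | -100 | +6.8 | -14.71 | +10,000 | +14.71 | -36 |
| Dearer, worse | +100 | +6.8 | +14.71 | -10,000 | -14.71 | -236 |

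Example of the last column, first row: 20 × 6.8 + 100 = 236.

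The table shows three things:
- In every row the raw-day ratio and the QALY ratio have opposite signs. Recoding to days saved aligns them.
- The first and last rows, dominant and dominated, share a value in every ratio column, including the QALY column and the recoded column. Recoding does not cure this.
- Net benefit separates all four rows.

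**Step 3: range.** For assumed costs of 50 to 200 the raw-day ratio has size 7.35 to 29.41 at 6.8 days and 5.95 to 23.81 at 8.4 days. The sign pattern is the same throughout.

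**Step 4: the third comparison.** Suppose NDVH costs 50 more than TAH and TLH 200 more, with VH and LAVH days standing in for NDVH and TLH.
- NDVH over TAH: 50/6.8 = 7.35 per day saved
- TLH over TAH: 200/8.4 = 23.81 per day saved
- TLH over NDVH: (200 - 50)/(8.4 - 6.8) = 150/1.6 = 93.75 per day saved

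Someone prepared to pay a little over 23.81 per day would accept both planned ratios. Neither ratio shows that the step from NDVH to TLH costs 93.75 for each further day. At 20 per day the pairwise net benefits are:
- NDVH over TAH: 20 × 6.8 - 50 = +86
- TLH over TAH: 20 × 8.4 - 200 = -32
- TLH over NDVH: 20 × 1.6 - 150 = -118

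**The case against.** The strongest reply is that no competent analyst would be misled. Incremental cost and incremental effect must both be calculated before they are divided, and their signs identify the quadrant. Cost, time to recover and QALYs are also trial outcomes in their own right, and the Objectives section leaves no doubt that faster is better. This stands against any claim that dominant and dominated routes cannot be told apart: they cannot be told apart from the ratio alone. It does not repair the stated formula. In addition, the Data analysis section compares cost by Kruskal-Wallis and QALYs by Kaplan-Meier and Cox methods. Neither yields the mean increments a reader would need beside the ratio.

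Several stronger readings are tempting but not supported:
- **That the smaller-is-better outcome causes the shared sign.** It does not. The QALY column above has the same property, and so does the recoded column.
- **That the protocol expects cheaper and faster routes, so the ratio is meaningless where it will be used.** Faster is hypothesised; a net saving is not. The Background says "Although direct costs appear to be high for TLH, a shorter postoperative hospital stay and lower indirect costs appear to make it more cost-effective", which stops short of lower total cost, and that "there has been no direct comparison of costs between VH and TAH". If TLH proves dearer and faster, that is a trade-off in which an ICER is meaningful.
- **That the lack of a dominance rule, intervals or acceptability analysis is a fault.** These may sit in the statistical analysis plan, which is not shown.
- **That no valid interval exists for the ratio.** Fieller and bootstrap methods are available, even if the interval can be awkward.
- **That the QALY denominator will often have the wrong sign.** A figure of 10-43% of trials follows from assumed utility gaps of 0.2-0.4 over 7 days, QALY SDs of 0.03-0.10 and 39 to 49 patients per arm. None of the utility or SD inputs is in the document, and the calculation attributes the whole QALY difference to 7 days of faster recovery. No weight is placed on it here.

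**Conclusion.** The point holds in a limited form. As stated, the recovery-time ICER reverses the usual sign convention. For a route better than TAH on both effects, it contradicts the QALY ICER in sign, whatever the size of the cost difference. This follows from the written formula and the outcome definition, with no assumption beyond a faster route having a negative increment (-6.8 days for VH, -8.4 days for LAVH on the planning means).

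Ratios formed only against TAH also fall short of the three-way comparison set as a primary objective. That the ratio alone does not identify the quadrant is true of every ICER and is a reason for reporting its components. It is not a defect peculiar to this trial.

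The unit costs, the 0.01 QALY and the 20 per day only illustrate signs and ordering; they predict nothing about this trial. The -8.4 days belongs to LAVH and should not be read as a TLH planning value. The trial data are unaffected, so the matter can be settled before analysis.

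**What to change.** 1. Define the first effect as recovery days saved, TAH minus route, so that both ICERs read as cost per unit gained.
2. Report mean incremental cost and mean incremental effect beside each ratio, and state dominant or dominated where that applies.
3. Add incremental net benefit, (value per unit × effect gained) - incremental cost, for each of the three pairs including TLH against NDVH. Give its interval over a stated range of values per day saved and per QALY.

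If the unseen statistical analysis plan already contains some of this, only the definition of the effect and the third comparison need aligning with it. The cost is a change of wording and a few lines of code; no new data are needed. The downside is that results are shown over a range of values instead of as one ratio, and the range per recovery day has to be chosen and justified, because the protocol supplies none.

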There is also a relative paucity of data on long-term outcomes; quality of life, urinary, bowel and sexual function in randomized controlled trials comparing surgical approaches to hysterectomy for which well-validated instruments on pelvic organ function would need to be applied in a standardised manner [2]. In addition, postoperative recovery and quality of life should be regarded as key outcomes in trials on approaches to hysterectomy for benign disease as these are the ultimate tests of effectiveness. To date there is no study which has considered quality of life, pelvic organ function and cost-effectiveness for the three main types of hysterectomy. The aim of this study is to provide evidence on the optimal type of hysterectomy in terms of cost-effectiveness by way of a three-armed randomized controlled trial (RCT) between NDVH, TLH and TAH in a low-resource setting.

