### Resource use and costs

Direct costs would include surgical costs, clinic costs, investigation costs and care during hospital stay. Surgical costs will consider staff cost, equipment cost, anaesthetic costs and cost of basic utilities; water, electricity and building cost. Clinic costs will entail staff cost, equipment cost and cost of basic utilities for clinics during the preoperative and postoperative period. Investigation costs will include laboratory and imaging costs for preoperative period and postoperative period. Information on routine investigations; full blood count, blood urea, serum electrolytes, urine full report, ECG, chest X-ray, transvaginal ultrasound scan (TVS) and any other additional investigation would be collected from clinic and in-ward medical records by the data collector on to a data sheet. The cost of hospital stay will include staff costs, cost of medicines and basic utilities. Information on healthcare costs were obtained from the medical supplies division of the Ministry of Health, Sri Lanka. Information on labour costs and basic utilities were obtained separately for each centre. Indirect costs will consider costs of additional investigations and medicines paid for by the patient, travel costs to and from the hospital/clinic, cost for carers and productivity losses for the patients and families and will be obtained by patient-filled questionnaires.

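### The planned ICERs compare NDVH and TLH only with TAH, so they do not by themselves rank the three routes as the primary objective requires; the direction of the recovery effect is also undefined

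*Protocol article*

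**What the plan says.** Under Primary objectives the protocol undertakes "To compare the cost-effectiveness of TLH versus NDVH versus TAH". The Background puts the goal more broadly: "The aim of this study is to provide evidence on the optimal type of hysterectomy in terms of cost-effectiveness". Both cover all three routes.

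The Economic evaluation section is narrower. It defines the ICER as "the incremental costs divided by the incremental effects (time to recover and QALYs gained", and calculates it "for the intervention groups (NDVH and TLH) over the standard care (TAH) group". The Methods part of the Abstract gives the same rule. No ICER of TLH against NDVH, ranking by cost with removal of dominated options, or net-benefit comparison is described.

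The effect named first in that ratio is time to recover. Outcome measures defines it as the "earliest time to resume all or a combination of activities done prior to surgery", so a smaller value is better. The Economic evaluation section does not say whether the increment is in days taken or days saved.

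The Data analysis section does plan three-arm and pairwise comparisons, but of recovery and QALYs (Kaplan–Meier and Cox) and of cost (Kruskal-Wallis with post hoc tests) separately. None of them joins cost and effect.

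**The concern.** A patient receives one of three routes, so the options are mutually exclusive. To choose among them on cost-effectiveness, each option has to be judged against the next less costly option still in contention. A ratio against TAH averages over the whole step from TAH to TLH. It can hide that most of the gain was already available from NDVH at lower cost, or that NDVH is poor value and should drop out.

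The Discussion says the findings should inform gynaecologists' practice and Ministry of Health resource allocation. If both alternatives look acceptable against TAH, the stated rule gives no basis for choosing between them.

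The direction of the recovery effect matters for a simpler reason. A negative ICER is usually read as dominance and a positive one as a trade-off. With an effect for which lower is better, those readings are reversed.

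**Working it through.** **Inputs.** The Sample size calculation section gives mean time to recover of 28.1 days for TAH, 21.3 for VH and 19.7 for LAVH. VH and LAVH stand in here for NDVH and TLH. The protocol states no cost, ICER or willingness-to-pay threshold, so it has no figure of its own to reproduce on this point, and every cost below is an assumption in arbitrary units.

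**Days saved.**
- NDVH versus TAH: 28.1 − 21.3 = 6.8
- TLH versus TAH: 28.1 − 19.7 = 8.4
- TLH versus NDVH: 21.3 − 19.7 = 1.6

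**Comparator set.** ICER = difference in cost / days saved.

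| Assumed extra cost over TAH (NDVH; TLH) | NDVH v TAH | TLH v TAH | TLH v NDVH | Full incremental reading |
|---|---|---|---|---|
| 50; 250 | 50/6.8 = 7.4 | 250/8.4 = 29.8 | 200/1.6 = 125 | All three stay; the relevant figure for TLH is 125 |
| 240; 250 | 240/6.8 = 35.3 | 29.8 | 10/1.6 = 6.25 | NDVH is extendedly dominated; the relevant figure for TLH is 29.8 |
| 10; 30 | 1.47 | 30/8.4 = 3.57 | 20/1.6 = 12.5 | All three stay; the relevant figure for TLH is 12.5 |
| −10; 30 | cheaper and faster | 3.57 | 40/1.6 = 25.0 | TAH is dominated; the relevant figure for TLH is 25.0 |
| 30; 20 | 30/6.8 = 4.41 | 20/8.4 = 2.38 | TLH cheaper and faster | NDVH is dominated |

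The plan would report the second and third columns. In the first row, any threshold between 29.8 and 125 per day makes both routes acceptable against TAH, yet NDVH is the better choice, because the step from NDVH to TLH costs 125 per day.

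With TLH at 250, the picture turns where NDVH costs 250 × 6.8/8.4 = 202.4 more than TAH. Below that, TLH versus NDVH exceeds 29.8; above it, NDVH is extendedly dominated. The gap can therefore go either way, and its size is set by costs that are not yet known.

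**Direction.** Taking time to recover literally, the increments are −6.8 and −8.4.
- A route costing 250 more and 8.4 days faster: 250/(−8.4) = −29.8. As days saved: +29.8.
- A route costing 50 less and 6.8 days faster: (−50)/(−6.8) = +7.4. As days saved: −7.4.

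On the literal reading the trade-off looks like dominance, and the dominant route looks like a trade-off.

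**The case against.** TAH as the reference is not arbitrary. It is the control arm, and the hypothesis is framed against it: "We hypothesize that TLH and NDVH are better than TAH in terms of time to recover". The Discussion also asks whether either alternative improves on TAH. That explains the two planned ICERs and justifies reporting them, but it does not remove the mismatch, because the primary objective and the aim go beyond the hypothesis.

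A reader might infer that the three-way objective cannot be answered. The documents do not support that. Both increments share the TAH arm, so TLH versus NDVH follows from the same data as the difference in extra costs divided by the difference in effects. What the plan lacks is the stated comparison, not the means to make it.

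A reader might also infer that the recovery ICER has the wrong sign. That holds only if the increment is taken as days elapsed. The text fixes no direction, and the word for gain in the ratio's definition could be read with both effects. The QALY ICER has no such problem. A sign convention could be settled in the statistical analysis plan that the protocol promises; the comparator set is different, because the protocol states it and it conflicts with the objective.

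Finally, occupation is among the activities that define recovery, while societal cost includes "cost for carers and productivity losses for the patients and families". A reader might infer that the same work days are counted on both sides of the ratio. Only partial overlap is possible: resuming work need not be what sets the recovery date, some women may have no paid work, and the losses include those of families. Removing productivity losses from one ratio would also depart from the stated societal perspective. This is not part of the point.

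**Conclusion.** The point holds as a mismatch between a stated objective and a stated analysis. The Economic evaluation section and the Abstract fix ICERs against TAH only, while the primary objective compares all three routes and the aim is to find the optimal one. The two planned ratios do not by themselves rank NDVH against TLH, and the separate tests of cost and effect do not fill that gap.

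The size cannot be fixed from the protocol. On the planning means the alternatives are 1.6 days apart. With an assumed 250 for TLH, the TLH-versus-NDVH ratio is 125 or 6.25 per day saved according to whether NDVH is assumed to cost 50 or 240 more than TAH, against 29.8 for TLH versus TAH. No single multiple should be taken from this: it rests on invented costs and on VH and LAVH as stand-ins. The same logic applies to the QALY ratio, for which the protocol gives no planning figures.

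The undefined direction of the recovery effect is a secondary, conditional fault that one phrase removes. The change should be made, but nothing here threatens the trial's design or data collection.

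**What to change.** In the Economic evaluation section, and in the matching sentence of the Abstract, replace the TAH-only rule with a full incremental analysis of all three arms: order the routes by mean cost, remove dominated and extendedly dominated options, and give each remaining option's ICER against the next less costly one. Net monetary benefit for all three arms is an equivalent way to state it. The ratios against TAH can stay as additional results for the stated hypothesis.

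Define the recovery effect as days of recovery saved, so that a positive value is a benefit, as it is for QALYs gained.

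Settle both before the database is opened, so that the comparator for a primary objective is not chosen after the results are seen. The cost is a change of wording and a little more analysis; no new data are needed.
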